### Assessment of efficacy

For the primary outcome, number and percentage of participants achieving biochemically validated, prolonged abstinence from smoking reported between a QD and 36 weeks gestation or childbirth, whichever is earlier, will be reported for each treatment group. For this outcome, smoking lapses are permitted during this period, provided no more than five cigarettes in total are smoked^38^ and a 7-day period of total abstinence is reported immediately before primary outcome follow-up. Reported abstinence will be validated by exhaled CO, saliva cotinine or saliva anabasine, with the actual measure used depending on abstinent participants’ reported use of NRT and/or e-cigarettes.

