**Methods and analysis:**

A two-arm parallel group, open-label, multicentre, assessor-blind randomised controlled trial. Participants are recruited at hospital antenatal clinics and other NHS settings throughout England and Wales or via social media advertising. Those enrolled are in antenatal care, <25 weeks’ gestation, smoke ≥5 daily cigarettes; accept referral for NHS stop smoking support and agree to set quit dates, try NRT and vape less than daily. Participants are randomised to: (1) usual care (UC) or (2) UC plus an intervention combining (1) NRT for preloading, (2) counselling to continue NRT during brief smoking lapses, and for those who cannot stop, (3) NRT to reduce smoking. The primary outcome is biochemically validated, smoking abstinence from 6 weeks after randomisation to 36 weeks gestation. Secondary outcomes include birth outcomes and cost per quality-adjusted life year. Questionnaires collect follow-up data augmented by medical record information. We anticipate quit rates of 10% and 15.9% in the control and intervention groups (OR=1.7). By recruiting 1430 participants, smoking, nicotine and pregnancy 3 should have 90% power (alpha=5%) to detect this effect. We will use the Economics of Smoking in Pregnancy model to estimate cost-effectiveness.

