## Outcomes

### Primary outcome

Biochemically validated, prolonged abstinence from smoking reported between 6 weeks after randomisation and 36 weeks gestation or childbirth, whichever is earlier.

Smoking lapses are permitted during this period, provided no more than five cigarettes in total are smoked and a 7-day period of total abstinence is reported immediately before primary outcome follow-up.

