### Sample size and justification

To detect a difference in smoking cessation in late pregnancy between control and intervention group proportions of 0.1 and 0.159, respectively, (OR of 1.70) with 90% power and 5% two-sided alpha requires 715 participants per arm (total n=1430). There is no adjustment for missing data; it will be assumed those lost to follow-up are smoking. Based on a recent SiP trial,^33^ assuming a quit rate in the UC group of 10% and anticipating an OR of 1.70 for the effects of NRT (1) as preloading and (2) continued in smoking lapses to facilitate return to abstinence. An OR of 1.7 is considered clinically important and plausible, based on the anticipated effect of *preloading*^17 34^ and *lapse prevention*^21 35 36^ intervention components. The third intervention component (*NRT for smoking reduction*) will not contribute to the primary outcome as this is offered to participants who have returned to smoking.

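### The primary outcome has two start points, 6 weeks after randomisation in its definition and a quit date in the efficacy section, and they can classify the same woman differently

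*Protocol article*

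**What the plan says.** Three places in the protocol article define the primary abstinence period.

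- Outcomes, Primary outcome: "Biochemically validated, prolonged abstinence from smoking reported between 6 weeks after randomisation and 36 weeks gestation or childbirth, whichever is earlier".
- Abstract, Methods and analysis: "The primary outcome is biochemically validated, smoking abstinence from 6 weeks after randomisation to 36 weeks gestation".
- Assessment of efficacy, which states what will be reported for each group: "biochemically validated, prolonged abstinence from smoking reported between a QD and 36 weeks gestation or childbirth, whichever is earlier".

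The definition and the efficacy section both attach the lapse allowance to the period they have just described. The definition has "Smoking lapses are permitted during this period, provided no more than five cigarettes in total are smoked", and the efficacy section has "smoking lapses are permitted during this period, provided no more than five cigarettes in total are smoked". Both also require 7 days of complete abstinence immediately before follow-up.

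Other sections bear on what a quit date is. Component 1 (preloading) has intervention participants choose one 1 to 4 weeks after their first counselling session. Usual care includes help with setting one but gives no interval. The 6-week questionnaire asks whether one was set. Component 2 (lapse recovery) foresees a new quit attempt after a failed one.

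**The concern.** This is the trial's only primary outcome, and the article gives it two start points. Because the five-cigarette cap is counted over the period, moving the start changes which cigarettes count and therefore who is a success.

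The two starts also differ in kind. Six weeks after randomisation is the same point in both arms and cannot be affected by treatment. A quit date is chosen after randomisation, in an open-label trial, and the preloading component deliberately schedules it in one arm. A period starting there may differ systematically in length and content between arms. It would also expose more of the time in which lapse recovery is meant to work, since lapses between the quit date and week 6 count against the cap only under the efficacy section.

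**Working it through.** **1. The definitions side by side**

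| Element | Primary outcome | Assessment of efficacy |
|---|---|---|
| Start | 6 weeks after randomisation | a quit date |
| End | 36 weeks or childbirth, if earlier | same |
| Lapse cap | 5 cigarettes in the period | same |
| Final 7 days | complete abstinence | same |

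Only the start differs. The abstract agrees with the Primary outcome section on it. No section equates a quit date with week 6 or ranks the two.

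**2. Do they classify women differently?** Two constructed cases, both with validated abstinence at 36 weeks:

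- Case A: quit date at week 3, eight cigarettes between weeks 3 and 6, none afterwards. Week-6 start: 0 cigarettes counted, 0 ≤ 5, success. Quit-date start: 8 counted, 8 > 5, failure.
- Case B: smoking beyond the cap after week 6, new quit attempt at week 10, abstinent from then. Week-6 start: failure. Quit-date start: success, if the later date may serve as the quit date.

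Case A is the kind of woman lapse recovery is meant to help. Case B rests on the new quit attempt foreseen in Component 2.

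**3. Window length.** Entry is below 25 weeks. Take the latest entry, 24 weeks 6 days (24.86 weeks):

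- Time to 36 weeks: 36 − 24.86 = 11.1 weeks.
- Week-6 start: 11.1 − 6 = 5.1 weeks, in either arm.
- Quit-date start, intervention arm, assuming the first session is on the day of randomisation: 11.1 − 1 = 10.1 down to 11.1 − 4 = 7.1 weeks.
- Quit-date start, usual care: not fixed by the article. It is 11.1 weeks at most, if a woman quits on the day of randomisation.

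These are extremes under stated assumptions, not expected values.

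**4. The plan's own sample size.** Inputs: 10% in usual care, OR 1.70, 90% power, two-sided 5%, 1:1 allocation.

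- p2 = (1.70 × 0.10/0.90) / (1 + 1.70 × 0.10/0.90) = 0.15888.
- n = [1.960 √(2p̄(1−p̄)) + 1.282 √(p1(1−p1) + p2(1−p2))]² / (p2−p1)², with p̄ = 0.1294. This rounds up to 682 per arm.
- With continuity correction, (n/4)[1 + √(1 + 4/(n(p2−p1)))]² gives 715 per arm.

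The stated 715 reproduces, and this point does not challenge it.

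**5. What might the choice do to power?** The documents give no reclassification rate. The shares below are assumptions. They suppose that 10% and 15.9% hold under one start and that some successes become failures under the other. Power at 715 per arm is Φ{[(p2−p1)√n − 1.960√(2p̄(1−p̄))] / √(p1(1−p1) + p2(1−p2))}, without continuity correction.

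| Successes lost, usual care / intervention | Rates | OR | Power |
|---|---|---|---|
| none / none | 10.0% / 15.9% | 1.70 | 91% |
| 10% / 10% | 9.0% / 14.3% | 1.69 | 88% |
| 20% / 20% | 8.0% / 12.7% | 1.68 | 83% |
| none / 10% | 10.0% / 14.3% | 1.50 | 70% |
| 10% / none | 9.0% / 15.9% | 1.91 | 98% |

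The effect can go either way. Case B would add successes rather than remove them, which the table does not cover.

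**The case against.** The best answer is that the article leans clearly one way. The formal definition and the abstract agree on week 6, the section that fixes the primary model offers no rival start, and the efficacy sentence is probably leftover wording. That stands as a guide to intent, but the article does not say so. A condensed article may omit detail, but here it states both versions.

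A colleague might also defend a quit-date start on substance. If the first session comes more than 2 weeks after randomisation and preloading lasts 4 weeks, the quit date falls after week 6 (2 + 4 = 6), and a woman who smokes more than five cigarettes between week 6 and her quit date fails under the week-6 rule. That is a real consequence of the formal definition. It is a case for a labelled sensitivity analysis, not for two primary definitions.

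Some stronger readings are tempting but not supported:

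- That the trial is powered on one rule and reported on the other. The sample size section refers only to cessation late in pregnancy and names no start.
- That power falls. Only assumed shares give that, and the reverse assumption raises it.
- That any woman without a quit date has no outcome. If she still smokes she is plainly a failure, and missing smoking data count as smoking. Only a woman who stops without setting a date is unclear.
- That Component 3 contradicts the sample size section, which says it "will not contribute to the primary outcome as this is offered to participants who have returned to smoking". Component 3 as described sets no quit date.
- That the conflict opens a post-hoc choice. The SAP is to be finalised before database lock and unblinding, so it can be settled blind.

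**Conclusion.** The contradiction is real and sits in the sole primary outcome, so it should be corrected. The efficacy section is the outlier. Cases A and B need no assumed rates to show that one woman can be counted differently under the two rules; case B does depend on allowing a later quit date to start the period.

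The quit-date version is also the weaker choice: it starts the period at a date set after randomisation, which need not be unique and which the intervention schedules. That the windows would differ between arms is plausible rather than shown, because the article gives no timing for usual care.

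The numerical effect is unknown in size and direction. The power figures under working, 70% to 98%, illustrate assumed shares of up to 20% lost and are not estimates. The SAP is not available here and may already use one start consistently.

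**What to change.** In Assessment of efficacy, replace the quit date with 6 weeks after randomisation as the start of the period. State that the five-cigarette count begins at 6 weeks after randomisation for every participant, whatever her quit date or number of quit attempts. Make sure the SAP uses the same start before database lock and unblinding. If a rate counted from a quit date is wanted, label it a sensitivity analysis and say which quit date is used and how a woman with none is handled.

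The cost is one sentence in the protocol and a check of the SAP. The main rule needs no new data and no change to the sample size. Recruitment is planned to run to June 2026 and follow-up to April 2027, so there is time to make the change blind.

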### Procedures for missing, unused and spurious data

For the primary analysis of the primary outcome and for other smoking-related secondary outcomes, participants with missing data will be considered to still be smoking; this is consistent with Russell Criteria, which defines standard smoking cessation study outcomes^38^ and has been proven a rational assumption in similar contexts.^39^ However, sensitivity analyses (described in detail in the SAP) will be conducted, which make different assumptions to investigate the potential impact of missing smoking abstinence data.

Analyses of other secondary outcomes will use available data, that is, with no imputation for participants with missing data.

### Safety

The study tests a behavioural intervention aimed at improving effectiveness of NRT use for smoking cessation in pregnancy. NRT is a standard NHS treatment and therefore we do not anticipate any harm being caused. We do, however, monitor any adverse events occurring during study participation. Data for pregnancy-related secondary outcomes listed above, and adverse events, separated by trial arm, will be reported to the DMC for their consideration. This will allow us to detect unexpected impact on the pregnancy and fetus to be detected and responded to while the trial is still ongoing. Although such impact is unlikely, it is important to stay vigilant to the possibility.

### Economic analysis

A cost-utility analysis will be performed from an NHS and Personal Social Services perspective^40^ using a previously published and peer-reviewed decision analytic model (DAM).^41 42^ Intervention costs, including staff time for training and intervention delivery, as well as costs associated with materials and prescriptions, will be collected alongside other trial data, and estimated at most recent price year to give a per participant cost for intervention and control arms. The DAM will be programmed with the following trial results; number of women included in intention-to-treat analysis, year of birth, average age of mother, cost per participant for intervention and control arms, and biochemically validated prolonged abstinence rates for intervention and control arms. The DAM will extrapolate trial results up to age 100 years for the mother and up to age 100 years for her offspring, including smoking behaviour, healthcare costs, life years gained and quality-adjusted life year (QALY). Primary measure of cost-effectiveness will be the incremental cost-effectiveness ratio (ICER) per QALY gained for combined mother and offspring lifetimes. Secondary measures of cost-effectiveness will be ICERs per additional quitter, per life year gained and per QALY gained, for mother and offspring outcomes at end of pregnancy and lifetime, both separately and combined. To control for uncertainty, the DAM will perform a probabilistic sensitivity analysis using 10 000 Monte Carlo simulations, which will estimate 95% CIs for ICERs, cost-effectiveness scatterplots and cost-effectiveness acceptability curves. To demonstrate return on investment, the DAM will estimate cost-offset ratios defined as the incremental healthcare savings (difference in healthcare costs between comparator and intervention groups plus incremental intervention costs) divided by incremental intervention costs, to estimate a return for every one Great British Pound (GBP) spent on the intervention.

### Patient and public involvement

A patient and public involvement (PPI) group has been involved in the trial design and throughout the study duration. The group consists of women who had experience of smoking during pregnancy. In the early stages of the intervention design, we interviewed five PPI group women who had experience of pregnancy and smoking. We discussed the proposed components and made changes to the intervention based on the comments and ideas brought by the PPI group. All interviewed thought NRT use for preloading and lapse recovery can be beneficial for pregnant people who wish to try and stop smoking. However, there was some concern about allowing women to use NRT throughout pregnancy without any focus on abstinence. In response to this point, the third intervention component was amended such that researchers will monitor participants’ heaviness of smoking and will stop NRT provisions if women admit smoking more heavily than at baseline or >10 daily cigarettes. This change was made to ensure a focus on reducing smoking when using NRT, rather than on ‘smoking as normal’.

During study set-up, representatives of the PPI group are being consulted on all aspects of the study, such as acceptability and accessibility of participant-facing documents, recruitment and retention methods, methods of data collection and the dissemination of findings. To ensure PPI involvement in the project’s strategic direction, two PPI representatives independent from the study team are invited to attend each TSC meeting.

### Ethics and dissemination

Ethics approval was granted by the West Midlands—Coventry & Warwickshire Research Ethics Committee (REC reference: 21/WM/0172; Protocol number 21011; IRAS Project ID: 291236). Approval for any protocol modifications will be sought from the REC/HRA and communicated to the funder and trial registry. Written informed consent will be obtained from all participants. Findings will be disseminated to the public, funders, relevant practice and policy representatives and other researchers. A data-sharing agreement has been written. Once the trial has finished and the main trial paper has been published, a de-identified data set will be available on reasonable request from the Nottingham Clinical Trials Unit.

### Trial and recruitment status

Recruitment began in May 2022 and is planned to continue until June 2026, and after all follow-up will be concluded, trial results are currently expected in mid-2027.

The study start was delayed by 1 year due to COVID-19, and implementation in the post-COVID NHS has been challenging; the timeline above includes a study extension. By 30 September 2025, 930 participants had been enrolled.

An ‘in trial’ pilot phase to demonstrate to funders that the full trial is deliverable was planned for the first 9 months of recruitment. Due to changes to the delivery of the NHS stop smoking care to pregnant women and COVID-19, at the end of the 9-month period, the trial did not reach the anticipated recruitment target of 385 participants. The NIHR Health Technology Assessment (HTA; the funder) reviewed the trial progress at that point, and the trial advanced beyond the pilot phase, with a further set of recommendations set up by the funder. Progression against the new targets was reviewed again 9 months later, and the trial team were invited to request a funded extension. The extension was granted in September 2023, for an additional 14 months of recruitment period, until December 2025. In August 2025, a further non-cost extension has been approved for an additional 6 months of recruitment. The recruitment end date is planned for 30 June 2026. The follow-up will continue for a further 10 months, with the participant’s last visit due in April 2027. There has been a marked improvement in site set-up and participant recruitment from 2023. Due to the COVID-19 pandemic, recruitment via the traditional routes became problematic; in response to those issues, early in the study we have developed alternative routes of recruitment online. We have successfully established and continue to use a pathway of recruitment via social media advertisement. We initially planned to open 26 recruiting sites, but after the review this was increased to 30 sites.

Protocol version: 5.0, 19 October 2023. For protocol changes see supplementary materials.
